## Abstract

**Introduction:**

Falls and fall-related injuries are a serious cause of morbidity and cost to society. Environmental hazards are implicated as a major contributor to falls among older people. A recent Cochrane review found an environmental assessment, undertaken by an occupational therapist, to be an effective approach to reducing falls. However, none of the trials included a cost-effectiveness evaluation in the UK setting. This protocol describes a large multicentre trial investigating the clinical and cost-effectiveness of environmental assessment and modification within the home with the aim of preventing falls in older people.

**Methods and analysis:**

A two-arm, modified cohort randomised controlled trial, conducted within England, with 1299 community-dwelling participants aged 65 years and above, who are at an increased risk of falls. Participants will be randomised 2:1 to receive either usual care or home assessment and modification. The primary outcome is rate of falls (falls/person/time) over 12 months assessed by monthly patient self-report falls calendars. Secondary self-reported outcome measures include: the proportion of single and multiple fallers, time to first fall over a 12-month period, quality of life (EuroQoL EQ-5D-5L) and health service utilisation at 4, 8 and 12 months. A nested qualitative study will examine the feasibility of providing the intervention and explore barriers, facilitators, workload implications and readiness to employ these interventions into routine practice. An economic evaluation will assess value for money in terms of cost per fall averted.

**Ethics and dissemination:**

This study protocol (including the original application and subsequent amendments) received a favourable ethical opinion from National Health Service West of Scotland REC 3. The trial results will be published in peer-reviewed journals and at conference presentations. A summary of the findings will be sent to participants.

**Trial registration number:**

ISRCTN22202133; Pre-results.

Strengths and limitations of this studyThe largest randomised controlled trial in an English setting to assess the clinical and cost effectiveness of a home environmental assessment and modification for falls prevention.Investigates the feasibility of recruiting participants from databases of participants previously assembled while conducting cohort, falls prevention randomised controlled trials.Hosts three ‘Studies within a Trial’, which will add to the evidence base about recruitment strategies and ways to minimise missing data within trials.Results will be generalisable to a community-dwelling population of older people within England.Uses an unblinded, patient self-report primary outcome measure; therefore, there is a possibility of reporting bias.

## Introduction

Falls in older people are common and can have serious consequences. Approximately 30% of people over the age of 65 years living in the community will have a fall each year.^1 2^ Around 85% of falls occur in the home.^3^ One-fifth of all falls are serious and require medical attention with 5% leading to a fracture.^4^ Fall-related fractures are a serious cause of morbidity and cost to society.^5^ Repeated falls commonly precipitate admission to institutional care and tend to be experienced by frail people in the older age range of 75 years and over.^1 6^ The number of falls is likely to increase due to an ageing population and will have a major impact on healthcare resource use, primarily due to hip fractures resulting from a fall. The importance of fall-related injuries has been recognised in the National Service Framework (NSF) for Older People^7^ and in the National Institute for Health and Care Excellence (NICE) Guidelines.^8^ The NSF calls for health improvement plans to be devised that will reduce the burden of fall-related injuries.

It is well recognised that many falls result from an interaction between environmental hazards and a broad array of medical conditions and physiological impairments.^9^ Environmental hazards are attributed by older people as primary factors in their falls and, thus, frequently cited in the literature as major contributors to falls. ‘Accident/environment’related factors were identified as the primary cause of just under one-third of falls in a review of 12 studies (mean of 31%, range 1%–53%, n=3628).^6^ Talbot *et al*
10 conducted a retrospective study and identified that ‘accident/environment’related factors were perceived by older people as the second most common cause of falls, with key environmental contributors identified as objects on floors, external forces and wet, uneven and icy surfaces.

The theoretical approach underpinning environmental assessment and modification is the person–environment–occupation (PEO) conceptual model of occupational therapy practice.^11^ This model posits that the person, environment and task being performed continually interact in ways that enhance or diminish a person’s occupational performance and that environmental hazards are dynamic entities that occur through the interaction between these three elements. The PEO model underpins occupational therapy practice that aims to maintain, restore or create a balance between these elements.^12^

The latest Cochrane review in this area (updated September 2012)^13^ found that environmental assessment and modification was an effective approach to reducing falls (relative risk of falling 0.88; 95% CI 0.80 to 0.96). It also concluded that the effectiveness of an environmental intervention was increased if delivered by an occupational therapist (OT). Current NICE guidance suggests that ‘older people who have received treatment in hospital following a fall should be offered a home hazard assessment and safety intervention/modifications by a suitably trained healthcare professional’. However, at the time of setting up the study, there was no guidance with respect to environmental assessment for people living in the community who are at elevated risk of falling but have not yet received hospital treatment due to a fall. Indeed, there has only been one UK trial of environmental assessment by an OT, which was a pilot study conducted by some of the authors.^14^ While this study showed no evidence of a difference between the randomised groups on the primary outcome of fear of falling, a statistically significant reduction was observed in the number of falls (a secondary outcome). Consequently, there is reasonable evidence to suggest OT delivered home hazard assessment and modification can lead to a reduction in falls. This large, multicentre trial builds on this previous work and aims to undertake a high-quality, adequately powered trial to evaluate the clinical and cost-effectiveness of an environmental assessment and modification, delivered by an OT, for the prevention of falls.

## Methods and analysis

### Trial design

The Occupational Therapist Intervention Study (OTIS) study is a modified cohort,^15^ pragmatic, two-arm, open, randomised controlled trial (RCT) with an economic evaluation and nested qualitative study. The cohort RCT (cRCT) design was chosen to avoid some of the key potential biases that can occur in a pragmatic trial, namely, high attrition and patient preference effects. In a cRCT, patients are recruited initially into a cohort, and there is usually an outcome run-in period. Given that outcome attrition occurs largely at the first follow-up time point, this attrition is largely avoided if an eligibility criterion for the randomised phase is completion of outcomes during the run-in period.^16^ With respect to preference effects, although the control group are aware of the possibility of being offered an intervention (in this case occupational therapy), they are unaware of when the actual randomisation occurs: this might avoid those biases, due to patient preference effects, which relate to timing of the offer of the intervention. In this study, the cRCT design was modified in that both intervention and control groups were told about the intervention prior to randomisation and that which group they would be in would be decided by chance/randomisation. In the cmRCT design, the process of obtaining patient information and consent aims to replicate that in real world routine healthcare, where patients are never told prospectively that their care options will be decided by chance. This approach partly replicates routine care in that the participant is not aware of when randomisation takes place and those in the control group are not aware of when they were formally allocated to be in the comparison group. Similarly, the intervention group are offered the intervention without having to face the possibility that once an offer has been made, that randomisation would withdraw the offer.

### OTIS main study aim

The main aim is to establish whether environmental assessment and modification delivered by an OT will lead to a reduction in the number of falls among those at elevated risk of falling living in the community.

### OTIS secondary aims

This includes:Establishing the cost-effectiveness of OT delivered environmental assessment and modification.Assessing the impact of the intervention on participants’ quality of life.Exploring the barriers and facilitators of implementing the trial’s findings among OT professionals and the wider community (eg, commissioners of services).

### Participants

#### Participant recruitment

One thousand two hundred and ninety-nine participants will be recruited by one of the following methods (see figure 1).

**Figure 1 F1:**
[figure not shown]
Flow chart of participants through the OTIS trial. GP, general practitioner; OT, occupational therapist; OTIS, Occupational Therapist Intervention Study; YTU, York Trials Unit.

#### Database search of existing cohorts held by the York Trials Unit (YTU) and the Yorkshire Health Study

The YTU has assembled a cohort of participants who originally participated in either the REFORM,^17^ SCOOP^18^ or CASPER^19^ trials and agreed to be contacted about future research studies run by the YTU. These studies recruited participants aged 65 years and over, from either routine National Health Service (NHS) podiatry clinics or GP practices. A database search of these cohorts and the Yorkshire Health Study cohort to identify participants over the age of 65 years^20^ will be undertaken to identify participants living in the OTs’ catchment area (Yorkshire and North Lincolnshire), who will be eligible for an invitation mailing. Participants known to live in a residential or nursing home will be excluded from the mail out. Potentially eligible participants will be sent an invitation pack asking if they would like to participate in the study. The pack will contain an invitation letter, participant information sheet, consent form, screening questionnaire and a prepaid envelope. In some cases, the person receiving the invitation pack may decline participation in the study, but a family member or friend may be interested in taking part. In such cases, the original recipient will be asked to pass on the research team’s contact details, so that the interested person can contact the study team.

#### GP practices and other services

To increase the generalisability of the study’s findings, participants will be recruited through GP practices in primary care. GP practices will be recruited to the study after a member of the study team or the local Clinical Research Network has contacted the practice and explained the study and the participants’ involvement. A database search will be undertaken to identify community dwelling men and women over the age of 65 who will be sent a recruitment pack. Patients known to have dementia or Alzheimer’s disease or who live in a residential or nursing home will be excluded from the mail out by the use of Read Codes (which are a coded thesaurus of clinical terms) and review of the patient’s address.

#### Opportunistic screening

Where there is capacity, opportunistic screening by other healthcare professionals (eg, GPs, Rapid Assessment Teams, chronic obstructive pulmonary disease nurses, Heart Failure Nurses, Community Matrons or NHS services (eg, ambulance services)) will take place. Potential participants will be given an invitation pack.

#### Advertising for participants

Radio, newspaper, faith magazine, social media or television advertisements may also be used to publicise the study and encourage potential participants to get in touch with the researchers. Additionally, posters or flyers may be placed within the geographical area of recruiting sites in places such as supermarkets, libraries and community centres.

Individuals identified via any of the four approaches described above who wish to take part in the study will be asked to return their completed consent form and screening questionnaire by post to the YTU. Researchers will assess the screening form for participant eligibility according to the study eligibility criteria. Participants deemed to be ineligible will be informed in writing. If the respondent is assessed as being ineligible because they have not had a fall within the past 12 months or do not report a fear of falling, but otherwise fulfil the eligibility criteria, they will be given the option to be rescreened in 4–6 months’ time.

All eligible, consenting participants will be asked to complete a baseline questionnaire and monthly falls calendars by post. Participants who return a valid baseline questionnaire and at least one falls calendar will be randomised into the trial. Participants can withdraw from the study at any point. The reason for withdrawal will not have to be declared; however, if provided, this will be recorded. Participants who do not wish to take part in the main study are not required to return any forms to the YTU.

### Inclusion criteria

Participants will be eligible for the OTIS trial if they:Are aged 65 years or over.Are willing to receive a home visit from an OT.Are community dwelling.Have at least one of the following risk factors for a fall in the next 12 months: either one fall in the past 12 months or report a fear of falling on their screening questionnaire.

### Exclusion criteria

Participants will be ineligible for the OTIS trial if they:Are unable to walk 10 feet today (3.05 m) even with the use of a walking aid.Are unable to give informed consent, for example, due to Alzheimer’s disease or dementia.Live in a residential or nursing home.Are unable to read or speak English and have no friend or relative to translate/interpret for them.Have had an OT assessment for falls prevention in the previous 12 months.Are on a waiting list for an occupational therapy assessment.Have not returned at least one completed falls calendar in the 3 months prior to randomisation.

### Randomisation

Participants will be enrolled into the study if they fulfil the eligibility criteria and provide written consent to take part in the study; they will then be randomised to either the intervention or control arm when they have returned a valid baseline questionnaire and at least one falls calendar within 3 months prior to the point of randomisation. Randomisation will be carried out using the YTU secure web-based computer randomisation service based on an allocation sequence generated by an independent data systems manager, who is not involved in the recruitment of participants. Participants will be randomly allocated to either the control group or the intervention group in a 2:1 ratio in favour of the control group (to reduce costs). Up to 12 participants from a particular site will be randomised at a time in a single block according to when sites state they have capacity to undertake intervention appointments and for how many participants. The allocation ratio used may go up to 3:1 in a block if the OTs have reduced capacity to carry out the assessment. The YTU will write to the participant’s GP informing them of study participation and to participants who are allocated to the intervention group.

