### Sample size

We propose to recruit and randomise 1299 participants to the OTIS trial in a 2:1 ratio (ie, 866 to usual care and 433 to intervention). This number allows for 10% attrition and provides 90% power (using two-sided significance at the 5% level) to show a difference in the percentage of participants who experience at least one fall in the 12 months following randomisation from 60% in the control group to 50% in the intervention group, accounting for the unequal randomisation (StataCorp. 2013. Stata Statistical Software: Release V.13). In the REFORM trial, previously conducted by some of the authors, an absolute difference of 5% was observed in the percentage of participants experiencing a fall (intervention group: 50%; control group: 55%), with a lower confidence limit of 13%; therefore, the decision was made to power this trial for a 10% absolute difference. In the event that sites are struggling with capacity to undertake assessments, we will consider using an allocation ratio of 3:1 (usual care to intervention) to reduce the number of participants they would have to see. If the final ratio was 3:1 (ie, 974 to the usual care and 325 to the intervention), we would have 85% power under the same conditions. The primary outcome is actually a count variable (number of falls, while proportion of participants experiencing at least one fall over the 12 months is a key secondary outcome); however, powering a trial for count data is more complex and requires greater assumptions and so a binary approach to the sample size calculation has been taken here.

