The environmental assessment will begin with an initial discussion about the participant’s history of falling, lifestyle, patterns of usage of areas in the home, risk-taking behaviour, strategies already adopted to reduce falls, environmental changes already in place prior to the assessment and functional vision. This will then be followed by the Timed Up and Go (TUG) test and an environmental assessment using the Westmead Home Safety (WeHSA) tool.^21^ The WeHSA was developed in Australia in 1997 for older adults and consists of a 57-item standardised, valid and reliable checklist of fall hazards in the following domains: internal/external traffic ways, general/indoors, living area, seating, bedroom, toilet, bathroom, kitchen, laundry, mobility aid, footwear, pets, medication management and safety call systems. The OT and the participant will move through the house together, and a functional assessment will be completed. Items on the checklist will be rated as either relevant (ie, deemed to be a hazard) or not relevant (ie, not deemed to be a hazard or not present). The OT will discuss any potential falls hazards identified by either the participant or the OT during the assessment and problem solve with the participant to engage them in identifying possible solutions. A list of recommendations will be agreed. If possible, any identified hazards will be removed. If required, the OT will make referrals to other agencies for equipment or a handyman for other minor modifications. They may also make recommendations for equipment that cannot be provided by social services, such as lightweight step ladders with handles and height adjustable rotary washing lines. In such cases, the OT will liaise with the client or a family member regarding purchase of such equipment. The OT will make a clinical judgement whether an additional home visit is required. Four weeks after the assessment, the OT or member of the OTIS research team will telephone the participant to check adherence to the recommendations.

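### Individuals are randomised to an intervention that alters the home, and no printed rule stops two people at one address from being split between the arms

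*Protocol article*

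**What the plan says.** **Unit of allocation.** The Randomisation section of the protocol article states: "Participants will be randomly allocated to either the control group or the intervention group in a 2:1 ratio in favour of the control group". It adds: "Up to 12 participants from a particular site will be randomised at a time in a single block". No household unit is described.

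**What is delivered.** Under OTIS trial intervention group, the therapist goes through the house with the participant, and where possible "any identified hazards will be removed". Equipment and minor building work can be arranged through other agencies. The same section says that the assessment also covers the participant's own fall-related behaviours.

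**Who can enter.** Under GP practices and other services, a search of the practice list is used to "identify community dwelling men and women over the age of 65 who will be sent a recruitment pack". Known dementia and care-home residence are screened out before mailing. Neither that section nor the Inclusion criteria and Exclusion criteria limit entry to one person per address. The exclusion for a recent occupational therapy falls assessment applies to the person, not to the home.

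**Awareness.** The Blinding section says that controls will not know when the intervention takes place. The Trial design section relies on controls not knowing when they were allocated.

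**Analysis.** The section on the primary outcome deals with clustering by therapist, as a sensitivity analysis. Household is not mentioned. The Sample size section has no allowance for contamination.

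**The concern.** A couple over 65 on the same practice list can both be mailed, both qualify and both be randomised. If one is allocated to the intervention and the other to usual care, the removed hazards and fitted equipment serve both. The control partner then receives part of what the trial is testing. Any benefit to that partner lowers the fall rate in the control arm and moves the estimated rate ratio toward one. In the economic evaluation, a fall prevented in that partner counts in favour of usual care.

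The control partner also sees a visit of about two hours in the home, which cannot be squared with the Blinding section. This matters because the article lists the unblinded, self-reported primary outcome as a limitation.

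**Working it through.** **1. Reproduce the plan's figure.** The Sample size section proposes to "recruit and randomise 1299 participants to the OTIS trial in a 2:1 ratio", that is 866 and 433, with 10% attrition, two-sided 5% significance and a change "from 60% in the control group to 50% in the intervention group". The stated power is 90%.

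The analysed numbers are 0.9 × 866 = 779.4 and 0.9 × 433 = 389.7. For two proportions with pooled variance under the null and no continuity correction:

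- pooled proportion = (2 × 0.60 + 0.50)/3 = 0.5667
- null SE = √[0.5667 × 0.4333 × (1/779.4 + 1/389.7)] = 0.03074
- alternative SE = √[0.60 × 0.40/779.4 + 0.50 × 0.50/389.7] = 0.03081
- z = (0.10 − 1.96 × 0.03074)/0.03081 = 1.290, so power = 90.1%

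The sample size needed for 90% power is 776 + 388 = 1164 analysed, or 1294 after dividing by 0.9, against 1299 stated. At 3:1 (974 and 325) power is 84.8%, against 85% stated. The plan's arithmetic is sound.

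**2. How often a pair is split.** With independent 2:1 allocation, two co-residents land in different arms with probability 2 × (2/3) × (1/3) = 4/9, or 44%. Within one block of 12 with 4 intervention places it is 2 × 4 × 8/(12 × 11) = 48%.

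**3. Share of controls exposed.** Let h be the share of participants who live with another participant. The article does not give h, so it is assumed. At 2:1, a control in a pair has an intervention partner with probability 1/3, so q = h/3 of all controls live in a modified home.

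**4. Dilution.** If the whole 10-point effect carries over, the control risk becomes 0.60 − 0.10 × q. This is the worst case. The intervention arm stays at 0.50.

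| h (assumed) | q | Exposed controls of 866 | Difference (points) | Power | N for 90% power |
|---|---|---|---|---|---|
| 0 | 0 | 0 | 10.0 | 90.1% | 1294 |
| 5% | 1.7% | 14 | 9.83 | 89.2% | 1339 |
| 10% | 3.3% | 29 | 9.67 | 88.1% | 1385 |
| 20% | 6.7% | 58 | 9.33 | 85.8% | 1489 |

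**5. Partial carry-over.** If half the effect carries over, q is in effect halved. The h = 10% row then becomes the h = 5% row (89.2%), and the h = 20% row becomes the h = 10% row (88.1%).

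These figures use the binary outcome, as the plan's own calculation does. The direction is the same for the primary fall rate, but its power is not calculated here.

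**The case against.** **The point rests on silence in a condensed article.** A household rule could sit in the full protocol or the randomisation specification. That is fair, and the point is limited accordingly. But the article does print the eligibility lists, unit of allocation, block size and permitted change of ratio. Followed as printed, these allow split households.

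**The family-member sentence does not create pairs.** A reader might infer from "a family member or friend may be interested in taking part" that the trial invites cohabitants together. It does not say so. It describes someone who declines and passes on the study's details, so one person replaces another. The support comes from the practice-list mailing and the absence of a limit per address.

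**The size is assumed and probably small.** Sample size for the SWATs plans on 10% of those mailed in the comparison group being randomised. If partners' uptake were independent, about 10% of participants with an invited partner would have a co-participant. If half of participants had such a partner (assumed), h would be 5% and power 89.2%. Couples may enrol together more often than that, which would raise h. Full carry-over is also too pessimistic, because the assessment addresses personal behaviours as well as the building. Both arguments stand and limit the size.

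**Treating co-residents as independent is nearly harmless here.** Under individual allocation, partners' assignments are about uncorrelated, so household correlation does not on average inflate the variance of the treatment effect. This stands. Household clustering matters only once households are allocated as units.

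**Loss of unawareness is local.** A reader might conclude that the design's protection against preference effects fails altogether. Only control partners in split pairs are affected. All participants already know of the intervention and that chance decides, and the Trial design section claims only that the approach might avoid such bias.

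**Conclusion.** The concern holds in a limited form. As printed, the plan randomises individuals to an intervention that changes a shared home, and nothing printed keeps co-residents in the same arm. Split pairs dilute the contrast toward no effect and conflict with what the Blinding section says of controls.

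The size is unknown because the number of shared households is not reported. For 5% to 20% of participants in such households, with full carry-over, the loss is about 1 to 4 percentage points of power (from 90.1% to between 89.2% and 85.8%). It is smaller with partial carry-over. The documents do not support a claim that the trial is seriously underpowered or that the sample size calculation is wrong. The remedy is worth making because it is cheap and recruitment is still in progress according to Trial status.

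**What to change.** **For remaining recruitment.** Allocate participants at the same address together as one unit and use robust standard errors clustered by household. Apply the rule before the first of the pair is randomised. Someone who comes forward later has a foreseeable allocation, so the rule should say how such a person is handled.

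**For participants already randomised.** Match on postal address, which is held because invitations, questionnaires and calendars go by post. Report the number of multi-participant households and of split households. Add a sensitivity analysis of the primary outcome that excludes all multi-participant households from both arms. Dropping only the exposed controls would remove co-residents from one arm and unbalance the comparison.

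**If a household rule already exists in the full protocol,** it is enough to state it and report the counts.

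**Cost.** A rule in the randomisation system, one cluster variable and a small loss of effective sample size. With share h in pairs and within-household correlation ρ, the variance inflation is about 1 + hρ. At h = 10% and ρ = 0.1 (both assumed) this is 1.01, and it cannot exceed 1.10 even at ρ = 1. Contamination at h = 10% would require 1385/1294 = 1.07 times the sample with full carry-over, or 1339/1294 = 1.03 with half. Joint allocation therefore costs less sample size unless ρ exceeds about 0.7 or 0.35 respectively, and it also removes the bias.
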